### Outcomes

The primary outcome measures are work participation as measured by the proportion of participants who have returned to work at 12-month follow-up and length of time before return to work (in days), work productivity (hours worked, work-related changes [i.e., reduced productivity, increased supervision, work content changes], and work stability [i.e., sickness absence after initial RTW and throughout the study period]). To provide descriptive information and group comparisons, an IQ estimate (Vocabulary, Similarities, Block Design, and Matrix Reasoning subscales of the Wechsler Adult Intelligence Scale–Fourth Edition) will be included at baseline (T1) only [34].

Postconcussive symptoms and quality of life will be used as secondary outcome measures at all time points (T1–T4), whereas outcome will also be measured in the domains of fatigue, sleep, emotional distress, self-efficacy, and cognition. The instruments that will be applied are listed in Table 1. Neuropsychological evaluation will not be conducted at T2.

**Table 1 Tab1:** Secondary and other outcome measures

Outcome measure	Measures
Secondary outcomes	
Postconcussive symptoms	Rivermead Post-Concussion Symptoms Questionnaire (RPQ) [31]
Quality of life	EuroQol five dimensions (EQ-5D) [48]
	Quality of Life After Brain Injury instrument (Qolibri) [49]
Other outcome measures	
Fatigue	Fatigue Severity Scale (FSS) [50]
Sleep	Insomnia Severity Index (ISI) [51]
Self-reported cognitive functioning	Cognitive Failures Questionnaire (CFQ) [52]
Emotional functioning (anxiety and depressive symptoms, posttraumatic stress symptoms, and self-efficacy)	The Patient Health Questionnaire (PHQ-9) [53]
	Generalized Anxiety Disorder seven-item (GAD-7) scale [54]
	Posttraumatic Symptom Scale (PTSS-10) [55]
	General Self-Efficacy Scale (GSS) [56]
Neuropsychological test measures	
Learning and memory	California Verbal Learning Test–Second Edition (CVLT-II) [57]
Prospective memory	Memory for Intentions Screening Test (MIST) [58]
Processing speed/executive function	Color Word Interference Test from the Delis-Kaplan Executive Function System (D-KEFS) [59]
	Trail Making Test (TMT) from the Delis-Kaplan Executive Function System (D-KEFS) [59]
	Coding from the Wechsler Adult Intelligence Scale–Fourth Edition (WAIS-IV) [34]
	Ruff 2 and 7 Selective Attention Test [60]
	Modified Six Elements Test from the Behavioral Assessment of the Dysexecutive Syndrome (BADS) (to be applied at T4 only) [61]

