### Sample size

Regarding RTW, an OR of 2.0 between the Compensatory Cognitive Training–Supported Employment (CCT-SE) and CG is regarded as the smallest relevant clinical and societal OR. Thus, the required total sample size calculated using G*Power is 110 (i.e., 55 persons in each group; α = 0.05, power level of 0.80) [39]. With an estimated loss to follow-up of 15% [40], 125 participants will be required. On the basis of an ongoing TBI study [41], we assume that this will be achievable within 12–18 months. An OR of 2.0 is equivalent to a 33% absolute difference in employment status between the two groups. According to [name] et al. [21], 50% of patients attained competitive work at 12-month follow-up. If the proportion of employed patients in the CG is 50% at 12-month follow-up, the proportion for the intervention group in this study will be expected to be 83% or above on the basis of the given estimation.

Two strategic samples will be drawn for the process evaluation, comprising 40 cases from the intervention group and 20 from the CG. It is a goal to achieve a heterogeneous sample with variation in severity of TBI, sex, age, type of job and workplace, company size, industry, and sector.

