### Statistical analysis

Descriptive statistics will be used to describe the baseline and injury characteristics of the variables related to participants and services. The *t* test will be used to analyze between-group mean comparisons for normally distributed continuous data, and the Mann-Whitney *U* tests will be used to analyze skewed data. For the primary outcome measures, a logistic regression model will be used to compare the proportions of participants returning to work at T4 in the CCT-SE and TAU groups, adjusting for other potential confounders. In addition, linear regression analysis will be applied to compare the difference in the mean length to RTW between the intervention groups at T4, adjusting for other potential confounders. For the secondary outcome measures, repeated measures analysis of variance will be used with time (T1–T4) as the repeated-measures factor and group (CCT-SE and TAU) being a between-group factor to test whether the CCT-SE intervention has a beneficial effect compared with TAU on RTW, symptoms, and functioning. The intention-to-treat principle will be applied for all proposed analyses.

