### Limitations

The present protocol has limitations that should be addressed. First, this is a pragmatic clinical trial in which the nature of the interventions prevents blinding of participants and therapists. Furthermore, outcome assessment will be performed by personnel unaware of group assignment. Second, the participants will be allocated to one of two groups, TAU or CCT combined with SE, potentially making it difficult to tease apart the active ingredients of the CCT-SE intervention. However, as mentioned previously, what makes this study innovative is the combination of rehabilitation and vocational science perspectives, in addition to strong cross-sectoral collaboration between specialized health care services and the welfare system. If we had decided to include a CG with traumatic injury but without head trauma, it would have been possible to identify nonspecific effects of traumatic injury that may contribute to symptoms and lasting functional impairment. The grant provided to us unfortunately prevents us from implementing this. Furthermore, the main aim of this study is to affect work participation through a combination of cognitive remediation and SE. For this purpose, a TAU CG seems appropriate because etiology and causation will be comparable across groups.

A third possible limitation is the risk of nonadherence to the interventions and losing patients to follow-up (i.e., risk of dropout). To facilitate study adherence and keep the dropout rates as low as possible, the research team will be well-trained, perform outreach, and be flexible with respect to timing of the intervention. Last, this trial is taking place in the southeastern region of Norway, and participants might not be representative of the whole population of Norway. It should also be mentioned that this is a single-center trial, which could potentially limit external validity. However, we are confident that the results could be generalizable, because more than half of the Norwegian population resides in this region.

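### Repeated-measures ANOVA over T1–T4, as ordinarily fitted, excludes anyone missing a visit; this sits badly with intention-to-treat for the secondary outcomes and wastes observed data

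*Protocol article*

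**What the plan says.** The Statistical analysis section of the protocol article states: "For the secondary outcome measures, repeated measures analysis of variance will be used with time" (T1–T4) as the within-person factor; group (CCT-SE or TAU) is the between-person factor. The paragraph closes with: "The intention-to-treat principle will be applied for all proposed analyses".

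The Outcomes section and Table 1 give the secondary outcomes as the Rivermead questionnaire, EQ-5D and Qolibri, all measured at each of the four visits. Neuropsychological tests skip T2, so the four-visit model mainly concerns the questionnaires.

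The Sample size section states: "With an estimated loss to follow-up of 15% [40], 125 participants will be required". The Limitations section lists "the risk of nonadherence to the interventions and losing patients to follow-up" and answers it with trained staff, outreach and flexible timing. The article names no imputation or likelihood method by which someone with a missing visit would stay in the ANOVA.

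**The concern.** Classical repeated-measures ANOVA needs a value at every level of the time factor. In standard software a participant without T4 is removed entirely, including the T1, T2 and T3 values already collected. The analysed set becomes those with complete visits, although the article wants all analyses to follow intention-to-treat and itself expects people to leave.

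The outcomes concerned carry the symptom part of the first hypothesis and the quality-of-life part of the second. Two things are at stake. One is precision, because collected data go unused. The other is possible bias, if those who leave differ from those who stay in a way that depends on the arm. Arm-dependent leaving is conceivable here: patients are not blinded, and contact differs by design (ten weekly group sessions plus up to six months of employment support, against usual care). The documents give no evidence that it will occur.

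**Working it through.** **Inputs from the article.** 125 enrolled, 1:1 allocation, 15% loss, four visits. The article's 125 is close to 110 × 1.15 = 126.5 (110 / 0.85 would be 129.4). I take 125 as it stands, since the difference does not bear on this point.

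**Participants excluded.**
- At the stated loss, 125 × 0.15 = 18.75, so about 19 are excluded. 125 × 0.85 = 106.25, so about 106 remain.
- If 5% also miss each of T2 and T3 (assumed), 0.85 × 0.95 × 0.95 = 0.767, and 0.767 × 125 ≈ 96 remain.
- If instead each of the three follow-up visits is missed independently (assumed rates), 5% gives 0.95³ × 125 ≈ 107, 10% gives 0.90³ × 125 ≈ 91, and 15% gives 0.85³ × 125 ≈ 77.

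**Precision, closed form for one case.** Suppose all correlations are 0.6, variances are 1, and 15% are missing at T4 only, at random.
- Variance of T4−T1 change: 2 × (1 − 0.6) = 0.80.
- Residual variance of T4 given T1–T3: 1 − 3 × 0.36 / (1 + 2 × 0.6) = 1 − 1.08 / 2.2 = 0.509.
- Share of the change explained by the observed visits: R² = 1 − 0.509 / 0.80 = 0.364.
- Variance ratio, completers to likelihood: 1 / (1 − 0.15 × 0.364) = 1.058, or about 6% more variance.

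**Precision, simulation.** Assumptions: 62 per arm, visit correlations 0.5–0.75, either equal or decaying over time. The comparator is a likelihood fit with unstructured covariance. The completers' change contrast had roughly 2–10% more variance with end-of-study dropout only, and about 10–28% more with 5% missed at each of T2 and T3 added.

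**Bias in the T4−T1 change contrast, simulation (about 13–15% dropout).**
- Random dropout (true effect −0.50 SD): completers −0.50, likelihood −0.50.
- Dropout linked to the last symptom score in the same way in both arms: completers −0.50, likelihood −0.50.
- Dropout after T3, linked to the T3 score in opposite directions by arm: the bias is proportional to corr(T3,T4) − corr(T1,T3). With equal correlations this is zero, and simulation gave 0.00 SD. With decaying correlations it was about 0.05–0.06 SD; for example, completers −0.343 and likelihood −0.397 for a true −0.40.
- Dropout possible at every follow-up visit, opposite by arm, correlations all 0.6, true effect −0.50: completers −0.54, likelihood −0.50. Here the error runs the other way, so its direction is not fixed.

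**The case against.** This is a condensed article, and how missing visits are handled is often settled in an analysis plan that is not shown. The ANOVA could be run on multiply imputed data, or the term could be used loosely for a mixed model. Either would keep everyone in. That stands as a caveat, but the point is not that a missing-data section is absent. The article names a method, and that method as ordinarily fitted excludes people whom the article says it will analyse.

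A reader might infer more than the documents support:

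- **That the plan breaks intention-to-treat.** The ANOVA still compares participants by allocated group, and the article does not define the term. The exclusion fits poorly with the promise; it is not a proven violation.
- **That only 96 of 125 will be analysed, against 106 with a T4 value.** The 96 needs 5% missed at each of T2 and T3, which the documents do not give. With pure dropout at the stated 15%, those with complete visits and those with T4 are the same 106 or so. What is lost is the earlier data of the other 19.
- **That the result will be biased by about a seventh of the effect** (0.057 / 0.40 = 14%). This needs dropout linked to symptoms in opposite directions by arm and correlations that decay.
- **That the T4 difference could be off by 0.19 SD.** One adverse simulation gave −0.31 against −0.50, but that is the raw T4 difference and not the group-by-time change that this ANOVA tests.

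It is also fair to say that the simulated dropout depended only on observed scores, the condition under which a likelihood model is unbiased. If leaving depends on an unobserved current state, the mixed model can be biased too. That is why its assumption should be stated.

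**Conclusion.** The concern holds in a limited form. For the secondary outcomes, the named model ordinarily leaves out about 19 of 125 participants at the article's own 15% loss, and discards data already collected from them. The cost in precision appears in every scenario simulated: small with end-of-study dropout alone (roughly 2–10% more variance), larger with some intermittent missed visits (about 10–28%, on the assumed 5% per visit). Bias is a possibility, not an expectation. It is near zero under random dropout or a dropout mechanism common to both arms, and about 0.05–0.06 SD in the change contrast under dropout opposite by arm with decaying correlations. All of these sizes rest on assumed correlations and dropout patterns. The logistic and linear regressions for return to work are outside the point. It should be changed because the better method is nearly free, not because the secondary results would otherwise be invalid.

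**What to change.** Replace the repeated-measures ANOVA with a linear mixed model for repeated measures: visit as a categorical factor, arm, visit-by-arm interaction, unstructured covariance, fitted by REML, including every randomised participant with at least one assessment. State that it assumes data are missing at random given the observed visits. Keep the completers' ANOVA only as a sensitivity analysis. If the full analysis plan already uses imputation or a mixed model, it is enough to say so.

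The cost is a sentence or two of wording and slightly more analysis work in standard software, with no new data. The change should be made before outcome data are seen by arm.

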**Methods/design:**

This study protocol describes an innovative randomized controlled trial in which we will explore the effect of combining manualized cognitive rehabilitation (Compensatory Cognitive Training [CCT]) and supported employment (SE) on RTW and related outcomes for patients with mild to moderate TBI in real-life competitive work settings. The study will be carried out in the southeastern region of Norway and thereby be performed within the Norwegian welfare system. Patients aged 18–60 years with mild to moderate TBI who are employed in a minimum 50% position at the time of injury and sick-listed 50% or more for postconcussive symptoms 2 months postinjury will be included in the study. A comprehensive assessment of neurocognitive function, self-reported symptoms, emotional distress, coping style, and quality of life will be performed at baseline, immediately after CCT (3 months after inclusion), following the end of SE (6 months after inclusion), and 12 months following study inclusion. The primary outcome measures are the proportion of participants who have returned to work at 12-month follow-up and length of time until RTW, in addition to work stability as well as work productivity over the first year following the intervention. Secondary outcomes include changes in self-reported symptoms, emotional and cognitive function, and quality of life. Additionally, a qualitative RTW process evaluation focused on organizational challenges at the workplace will be performed.

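### The four-visit repeated-measures ANOVA for secondary outcomes uses complete cases unless visits are imputed, does not match the cognitive-test schedule, and wrongly takes in return to work

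*Protocol article*

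**What the plan says.** All references are to the protocol article.

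- **Statistical analysis, model.** For the secondary outcomes, "repeated measures analysis of variance will be used with time (T1–T4) as the repeated-measures factor and group (CCT-SE and TAU) being a between-group factor". The stated purpose is "to test whether the CCT-SE intervention has a beneficial effect compared with TAU on RTW, symptoms, and functioning".
- **Statistical analysis, population.** "The intention-to-treat principle will be applied for all proposed analyses".
- **Statistical analysis, primary outcomes.** Return to work at T4 is assigned logistic regression, and time to return to work is assigned linear regression.
- **Outcomes, text.** Postconcussive symptoms and quality of life are secondary outcomes measured at all of T1 to T4. For the cognitive tests, "Neuropsychological evaluation will not be conducted at T2".
- **Outcomes, Table 1.** One test is listed as "Modified Six Elements Test from the Behavioral Assessment of the Dysexecutive Syndrome (BADS) (to be applied at T4 only".
- **Abstract, Methods/design.** "A comprehensive assessment of neurocognitive function, self-reported symptoms, emotional distress, coping style, and quality of life will be performed at baseline, immediately after CCT", which is the T2 visit. The abstract also counts change in cognitive function among the secondary outcomes.
- **Sample size.** 125 participants are to be enrolled, with an estimated 15% loss to follow-up.

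**The concern.** The model as worded raises three difficulties.

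1. **Missing visits.** Standard repeated-measures ANOVA needs a value at every level of the time factor for each participant. Someone who misses one visit contributes nothing, even with three observed scores. That sits badly with a commitment to intention-to-treat and a planned loss of 15%. If the chance of missing a visit depends on earlier symptoms or scores, the completers are a selected group and the estimated effects on symptoms and quality of life may be biased.
2. **Schedule.** A T1 to T4 factor presupposes four measurements. The cognitive tests do not have them, yet improved cognition is part of the first main hypothesis.
3. **Return to work.** The sentence on secondary outcomes gives a primary outcome a further analysis, of a type that does not suit a binary status.

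The symptom, quality-of-life and cognition results are at stake. The two regressions named for the primary outcome do not depend on this sentence.

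**Working it through.** **Inputs.** From the Sample size section: 125 to be enrolled and 15% loss to follow-up. From Statistical analysis: four time levels. Not in the document, and therefore assumed over a range: a further proportion *m* missing each of T2 and T3, independently, with *m* = 3%, 5% or 10%.

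**The plan's own figure.** The required 110 becomes 125 after allowing for loss. Dividing gives 110 / 0.85 = 129.4, so 130; multiplying gives 110 × 1.15 = 126.5, so 127. Neither returns exactly 125, which corresponds to a loss of 1 − 110/125 = 12%. That is a separate matter; only the 125 and the 15% are used below.

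**Participants with all four visits.** Complete cases = 125 × (1 − 0.15) × (1 − *m*)².

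| *m* at each of T2 and T3 | Calculation | Complete | Excluded |
|---|---|---|---|
| 0 | 125 × 0.85 = 106.25 | about 106 | about 19 (15%) |
| 3% (assumed) | 106.25 × 0.97² = 99.97 | about 100 | about 25 (20%) |
| 5% (assumed) | 106.25 × 0.95² = 95.9 | about 96 | about 29 (23%) |
| 10% (assumed) | 106.25 × 0.90² = 86.1 | about 86 | about 39 (31%) |

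Only the first row follows from the document. It is an upper bound on the ANOVA sample at that loss rate.

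**Missing-data assumption.** Analysing completers is in general unbiased only if missingness is unrelated to the outcome history. A likelihood-based mixed model allows missingness to depend on observed scores (missing at random). With baseline as a covariate it keeps each participant who has a baseline score and at least one follow-up score.

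**Schedule against the time factor.**

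| Measure | T1 | T2 | T3 | T4 | Fits a four-level factor? |
|---|---|---|---|---|---|
| RPQ, EQ-5D, Qolibri | yes | yes | yes | yes | Yes |
| Neuropsychological tests | yes | no | yes | yes | No, three levels |
| Modified Six Elements Test | no | no | no | yes | No, nothing repeated |

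The abstract places neurocognitive assessment at 3 months; the Outcomes section rules it out at T2. Both cannot be right.

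**Return to work.** The Outcomes section makes it a primary outcome: a proportion at 12 months, plus days to return. Eligibility requires sick-listing of at least 50% at 2 months after injury, so work status has little or no variation at T1. The same paragraph of Statistical analysis has already given this outcome two regression models.

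**The case against.** **Missing data.** The article does not prescribe deletion of incomplete cases. Intention-to-treat concerns analysing people in the arm to which they were randomised, and imputation before the ANOVA would be compatible with it. How missing visits are handled is often left to an analysis plan, and none is shown. This stands: a reader might infer that the plan flatly contradicts intention-to-treat, but the documents support only a conditional statement. What remains is the choice of a method that needs imputation to keep everyone, when one that does not is readily available.

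**Cognition.** Table 1 puts only RPQ, EQ-5D and Qolibri under its secondary-outcomes label, and all three are measured at four visits. The t test or Mann-Whitney test named in the same section could serve a T4-only measure, and a T1, T3, T4 version of the ANOVA is an obvious adaptation. So the analysis is not unusable in general; it runs as written for those three instruments among completers. But the abstract calls cognitive function a secondary outcome and the ANOVA sentence extends to functioning, so the mismatch is real.

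**Return to work.** It may be a stray word in a clause of purpose, since no primary analysis rests on it. That is fair, and it still needs deleting.

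**Stronger readings that do not hold.** A reader might argue that averaging the group effect over T1 to T4 dilutes it to 75%, because baseline is included. That presumes a test of the group main effect, which the plan never names; the group-by-time interaction would not be diluted in this way. Nor does unequal spacing of visits by itself break sphericity, for which standard corrections exist.

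**Conclusion.** The point holds as an improvement to the secondary analysis together with three wording corrections.

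- **Size.** At the protocol's own 15% loss, standard four-visit ANOVA uses at most about 106 of 125 participants. Under the assumed additional missed visits it uses about 100 to 86. No single figure in that lower range should be read as the plan's own.
- **Condition.** The exclusion of randomised participants applies unless missing visits are imputed, which a document not shown might specify. That dropout would depend on symptoms or work status is plausible but not documented, so no amount or direction of bias can be given.
- **Unconditional.** The T1 to T4 factor does not match the cognitive-test schedule, the abstract and the Outcomes section disagree about T2, and return to work does not belong in the sentence.

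The regressions planned for the primary outcome are unaffected.

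**What to change.** 1. Replace the ANOVA with a linear mixed model for repeated measures on all available visits, with visit, group-by-visit and baseline score as fixed effects. State the group difference at T4 as the contrast of interest.
2. For the neuropsychological tests, model T3 and T4 with the baseline score as covariate.
3. For the Modified Six Elements Test, use a simple between-group comparison or a regression on group at T4.
4. Remove return to work from the sentence; its analyses are already stated.
5. Align the abstract with the Outcomes section, so that neurocognitive testing is not implied at T2, and settle whether cognitive function is a secondary or an other outcome.

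**Cost.** Wording only, with no new data or visits. The mixed model takes slightly more analysis work and still relies on missing at random, which cannot be verified from the data.
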